## Abstract

**Background:**

Attentional function is the basis of cognitive function, and its decline affects the daily lives of older adults. Previous studies have not consistently reported the effects of dual-task training (DTT) on attentional function in community-dwelling older adults. This study aims to verify the effectiveness of DTT by combining “motor tasks” and “cognitive tasks involving motor activity” with a focus on inducing dual-task interference (DTI).

**Methods:**

The study design is a randomized controlled trial. The intervention consists of DTT that combines “motor tasks” involving lower limb movements with “cognitive tasks involving motor activity” incorporating complex finger movements. The program will be implemented in a DTI setting, and tasks will be adjusted individually for each participant. The intervention group will be conducted twice per week for four weeks, with each session lasting one hour. The control group will continue with the participants’ usual daily activities for four weeks. Attentional function will be assessed as the primary outcome using the Trail Making Test-Japanese and as secondary outcomes using the digit span test and the Stroop and reverse-Stroop test. Balance function will be measured using the single-leg stance test. All evaluations will be conducted at baseline and post-intervention. In the statistical analysis, paired *t*-tests will be used to compare pre-intervention and post-intervention changes within each group, and analysis of covariance will be used to compare intervention effects between groups.

**Discussion:**

Based on the study objectives, the maintenance and improvement of attentional function should be promoted to help community-dwelling older adults maintain healthy lives in familiar environments.

**Trial registration:**

UMIN, UMIN000057681. Registered on 30 June 2025. UMIN website https://center6.umin.ac.jp/cgi-open-bin/ctr/ctr_view.cgi?recptno=R000065882.

## Administrative information

Note: the numbers in curly brackets in this protocol refer to SPIRIT checklist item numbers. The order of the items has been modified to group similar items (see http://www.equator-network.org/reporting-guidelines/spirit-2013-statement-defining-standard-protocol-items-for-clinical-trials/).

## Introduction

### Background and rationale {6a}

Through attentional function, individuals select appropriate information from senses, memory, and thoughts. Attentional function forms the basis of various cognitive functions, including orientation, memory, and comprehension [1]. Attentional function is known to peak around the age of 20 and gradually decline with age [2, 3]. This decline leads to difficulties in instrumental activities of daily living (IADLs), such as managing finances [4] and performing laundry [5]. Furthermore, the decline is associated with an increased risk of falls [6, 7] and motor-vehicle accidents [8, 9]. Therefore, preventing the decline of attentional function is a crucial challenge for promoting independent living in older adults.

Dual-task training (DTT) is an intervention designed to enhance attentional control during multitasking. In this training, individuals are required to perform multiple tasks, such as motor and/or cognitive tasks, simultaneously. It has been reported to improve attentional impairments associated with cerebrovascular disorders and traumatic brain injury [10–12]. To maximize the effectiveness of DTT, task difficulty should be individually adjusted based on Dual-Task Interference (DTI) [12, 13]. In DTI, performance deteriorates when two tasks are performed simultaneously, even though each task is manageable when performed alone. Because the effectiveness of DTT is diminished when the level of interference is either too high or too low, an appropriate level should be identified for each individual.

Reviews on DTT for community-dwelling older adults have shown benefits in maintaining their general cognitive function and improving their balance function [14, 15]. However, findings regarding the effects of DTT on attentional function remain inconsistent. Most of the studies that have included attentional function as an outcome measure [16–25] did not report significant improvements, and only three studies [18, 21, 25] demonstrated statistically significant improvements. A common feature of these three studies is that they implemented DTT combining “motor tasks” and “cognitive tasks involving motor activity.” However, four other studies that incorporated similar components [17, 20, 22, 23] did not find improvements in attentional function. Although these studies had no substantial differences in sample sizes (20–50 participants) or intervention durations (1–3 months), inconsistency in outcomes may reflect differences in how task difficulty was appropriately adjusted based on DTI. Moreover, these studies relied on a limited set of measures and comprehensive evaluation of multiple domains of attentional function was lacking. Therefore, studies have not investigated the effectiveness of DTT that combines “motor tasks” and “cognitive tasks involving motor activity,” individually adjusting task difficulty based on DTI for improving attentional function in community-dwelling older adults.

### Objectives {7}

This study aims to determine the effectiveness of a DTT program in enhancing attentional function in community-dwelling older adults. In this DTT program, “motor tasks” and “cognitive tasks involving motor activity” are combined, and task difficulty is individually adjusted based on DTI. This program will be evaluated through a randomized controlled trial (RCT).

### Trial design {8}

The study design is an RCT, in which the DTT is compared to a control group of participants who maintain their usual daily routine. The allocation ratio is 1:1. The superiority of DTT compared to the control group will be tested.

## Methods: participants, interventions, and outcomes

### Study setting {9}

Participants will be recruited from community-dwelling older adults living in Kagamiishi Town, Fukushima Prefecture, Japan. The study will be conducted at the Kagamiishi Town Health and Welfare Center.

### Eligibility criteria {10}

The inclusion criteria will be as follows:Individuals aged 65–80 yearsIndividuals who can complete the Trail Making Test Part A (TMT-A) error-free within 40 to 80 sIndividuals who can participate in the intervention twice weekly for four weeksIndividuals who have provided informed consent to participate in the study

The age limitation in (1) was applied in consideration of the decline in attentional function with aging. The TMT-A criterion in (2) was based on reference values from the Trail Making Test-Japanese (TMT-J) manual [26], which reports a maximum score of 80 seconds among healthy older adults. Scores below 40 seconds were considered indicative of an adequate attentional function which is unlikely to improve further through intervention. Based on these considerations, the TMT-A criterion was established.

The exclusion criteria will be as follows:Individuals who have been medically advised to restrict physical activities, including those with conditions such as severe hypertension, cardiac diseases, or undergoing treatment for fractures that require exercise limitation.

### Who will take informed consent? {26a}

The principal investigator will explain the study objectives and procedures to all participants and obtain their written informed consent prior to enrollment. Through the participant information, the participants will be informed that all study data will be handled with strict confidentiality.

### Additional consent provisions for collection and use of participant data and biological specimens {26b}

Additional consent will be obtained if the stored data are to be used in a new study upon the completion of the study.

## Interventions

### Explanation for the choice of comparators {6b}

Through the trial, the attentional function of the intervention and control groups at baseline and post-intervention will be assessed to determine the effectiveness of DTT. The control group will consist of community-dwelling older adults living in the same area. They will continue their usual daily activities throughout the study period. As an ethical consideration, participants in the control group will have the opportunity to experience the DTT intervention after the study is complete.

### Intervention description {11a}

The DTT consists of a combination of “motor tasks” and “cognitive tasks involving motor activity”, and task difficulty is individually adjusted based on DTI. The intervention will be conducted at the Health and Welfare Center in Kagamiishi Town. It will be delivered by two occupational therapists who are well-versed in DTT with the assistance of two volunteers for operational support. The intervention will be implemented twice per week for four weeks, with each session lasting one hour. To facilitate implementation in community settings, DTT will be conducted with a group of approximately 30 participants.

Each one-hour session consists of a 5-minute health check, 10-minute warm-up exercises, 15-minute DTT, a 10-minute break, another 15-minute DTT, and a 5-minute cool-down. The specific tasks used in the intervention are presented in Table 1. In the DTT, participants will first practice “motor tasks” and “cognitive tasks involving motor activity” as single tasks. After they are accustomed to performing each task individually, they will perform two tasks simultaneously.

**Table 1 Tab1:** Examples of DTT task combinations

Motor tasks [18, 21, 22]	Cognitive tasks involving motor activity
・Stepping in a seated position ・Stepping in a standing position	■Finger exercises [21, 25] ∙ Perform combinations of hand gestures, such as rock and paper, rock and scissors, and scissors and paper, with both hands ∙ Perform different hand gestures simultaneously with each hand, such as rock with one hand and paper with the other ∙ Perform complex bilateral movements, alternating between the extension of the thumb on the one hand and the extension of the little finger on the opposite hand
・Stepping in a seated position ・Stepping in a standing position	■Upper limb exercises [17, 18, 21] ∙ Move both upper limbs in the instructed direction ∙ Move both upper limbs in the opposite direction of the instruction ∙ Perform vertical movements with one upper limb and triangular movements with the other ∙ Switch the roles of the upper limbs midway through the task
・Stepping in a seated position ・Stepping in a standing position	■Exercises using tools [18] ∙ Toss and catch a beanbag with one hand ∙ Toss and catch one beanbag with both hands ∙ Toss and catch two beanbags simultaneously with both hands

DTI setting is applied to both tasks. For “motor tasks,” if stepping in a seated position is performed with ease, the task will progress to stepping in a standing position. For “cognitive tasks involving motor activity”, participants will start with low-difficulty tasks, such as simple finger movements, and progress to higher-difficulty tasks when they can easily perform the low-difficulty tasks. Adjustments to task difficulty will be made at the discretion of the occupational therapist. If a task is judged to be too easy for the participant, the therapist will encourage progression to a more challenging level of the task to ensure an appropriate training load. To prevent falls, stepping in a standing position is performed in front of a chair with handrails or other stable supports placed nearby.

### Criteria for discontinuing or modifying allocated interventions {11b}

Criteria for discontinuing the intervention for participants include adverse events that permanently prevent their participation in the intervention.

Discontinuation will be considered in the following cases:Difficulty performing the exercises owing to a significant decline in motor or cognitive function.Inability to participate owing to hospitalization for medical treatment.Physician-imposed medical restrictions on participation owing to outpatient care.

### Strategies to improve adherence to interventions {11c}

Incentives will be provided to the participants to promote their adherence. Participants in the intervention group will receive 500 yen for attending each session. Those who attend all sessions including pre-intervention and post-intervention evaluation (10 out of 10) will receive a total of 5000 yen, while those who attend 8 out of 10 sessions will receive 4000 yen. Participants in the non-intervention group will receive a fixed payment of 5000 yen for completing the post-intervention evaluation.

### Relevant concomitant care permitted or prohibited during the trial {11d}

All types of care will be permitted during the study, other than non-scheduled DTT.

### Provisions for post-trial care {30}

In the event of any health damage to a participant during the study, appropriate treatment will be provided within the scope of public medical insurance coverage. The principal investigator is enrolled in the Occupational Therapist Comprehensive Compensation Insurance System to provide compensation as needed.

### Outcomes {12}

The following outcomes will be assessed at two time points, t0 and t2, as shown in Table 2, and differences in the change scores between the groups will be analyzed.

**Table 2 Tab2:**
[figure not shown]
Participant timeline

Time point

t0: baseline

t1: week1–week4

t2: week5

### Primary outcome assessment

To evaluate attentional function, the TMT-J [26] will be used. TMT-J consists of Part A (TMT-A) and Part B (TMT-B). In TMT-A, circles numbered from 1 to 25 are presented, and participants were instructed to quickly connect numbers in ascending order by drawing lines. In Part B (TMT-B), the circles contained either numbers from 1 to 13 or the first 12 characters of the Japanese Hiragana alphabet. Participants are instructed to connect the numbers and characters in alternating order. The time required (in seconds) for each test will be measured and used as an outcome indicator. Additionally, ΔTMT will be calculated by subtracting the time for TMT-A from that for TMT-B (ΔTMT = TMT-B − TMT-A). TMT-A is used to assess sustained attention, while TMT-B is used to evaluate divided attention, with shorter completion times indicating better performance. Additionally, smaller ΔTMT values indicate better executive function. Errors made during the tests will be recorded and included in the analysis as appropriate.

### Secondary outcome assessment

Attentional function will be comprehensively assessed using the digit span test [27, 28], and the Stroop and reverse-Stroop test [29].

The digit span test is a subtest of the Wechsler Memory Scale-Revised (WMS-R), a neuropsychological test designed to assess different memory functions in individuals. It is used to evaluate attention function and attention capacity. Participants are asked to repeat numbers spoken by an examiner in either forward or reverse order. The digit span ranges from three to eight digits, with two trials conducted at each span. If the participant responds correctly on either trial, the task proceeds to the next span. If a participant answers incorrectly twice, the test is terminated. The total score ranges from 0 to 24, with higher scores indicating better performance.

The Stroop and reverse-Stroop test will be used to evaluate the selective attention and attention capacity related to inhibition. The tasks consist of the following four types: (1) Control Condition 1 (selecting color patches corresponding to the meaning of color terms in black ink), (2) Reverse Stroop Condition (selecting color patches corresponding to the meaning of color terms), (3) Control Condition 2 (selecting color terms corresponding to color patches), and (4) Stroop Condition (selecting color terms corresponding to ink colors). Each task will be presented on an A4 paper with 60 trials, and performance will be evaluated based on the number of correct responses within 40 seconds.

To evaluate balance function, the single-leg stance time with eyes open and closed will be measured [30]. This measurement will be taken to assess static standing balance function through an evaluation of whether an individual can maintain balance within a narrow base of support. Further, balance function has been reported to be related to attention [31, 32] and is useful for evaluating physical functions affected by attention. Single-leg stance is measured from the moment a participant’s feet leaves the floor until one of the following occurs: the raised foot touches the floor, the raised foot touches the supporting leg, the position of the supporting foot shifts, or the hands touch the wall. Measurements are conducted for a maximum of 60 seconds, under both eyes-open and eyes-closed conditions. Shorter stance times indicate greater impairment in balance function. When the participants’ eyes are closed, the reduction in their visual input increases the difficulty of the task, often resulting in shorter stance durations than those in the eyes-open condition.

## Participant timeline {13}

### Sample size {14}

We calculated the required sample size as 60 participants based on the results of previous studies on TMT-A and TMT-B [16–18, 21]. We expected a 15-second difference in change scores (post–pre) between the two groups on the TMT-A, with a standard deviation (SD) of 15 seconds. This corresponds to an effect size of 1. Assuming a two-sided α of 0.05 and a statistical power (1–β) of 0.80, the required sample size is 34 participants (17 per group). Next, for TMT-B, we expected a 20-second difference in change scores (post–pre) between the two groups, with a SD of 25 seconds. This corresponds to an effect size of 0.8. Assuming a two-sided *α* of 0.05 and a statistical power (1–β) of 0.80, the required sample size is 52 participants (26 per group). Therefore, the final sample size was determined as 60 participants, considering the potential dropouts.

### Recruitment {15}

Participant recruitment will be conducted by placing advertisements in local media (e.g., public relations publications) and by posting flyers in public spaces within the community. This recruitment strategy has been proven successful in previous projects [33].

## Assignment of interventions: allocation

### Sequence generation {16a}

To ensure equal sample sizes, we will conduct allocation using block randomization. The randomization sequence, with a block size of four, will be produced using computer-generated random numbers (Microsoft Excel, Microsoft Corp., Redmond, WA, USA) by the principal investigator. No stratification of participants will be performed in this study.

### Concealment mechanism {16b}

After the baseline assessment, participants who meet the eligibility criteria will be randomly assigned to the intervention and control groups. The allocator will record the participants’ IDs in an Excel sheet and provide each participant with their group assignment in a sealed envelope. To ensure blinding, recruitment staff, data collectors, and statisticians will remain blinded to the group and will not have access to allocated information.

### Implementation {16c}

The allocation sequence will be generated by the principal investigator, and participant enrolment and intervention assignment will be conducted by a co-investigator.

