## Oversight and monitoring

### Composition of the coordinating centre and trial steering committee {5d}

This is a single-centre study designed, implemented, and coordinated at Fukushima Medical University. Day-to-day support for the trial is provided by the following staff:Principal investigator: Supervises the trial, conducts trial registration and participant enrolment, obtains informed consent, and ensures that the follow-up is conducted in accordance with the protocol.Data manager: Organizes data acquisition and safeguards the quality of the data.Data collectors: Conduct data acquisition, including assessments of attention and balance functions.Statistician: analyzes data after trial completion.

The principal investigator, data manager, data collectors, and statistician will meet before, during, and after the trial.

In this study, no formal independent committees, such as a steering committee or a data monitoring committee, will be established owing to the fact that it is a single-centre study with a low-risk, non-invasive intervention.

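### Allocation concealment is not assured by the roles as written: the author of the sequence also takes consent, and two sections name different enrollers

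*Protocol article*

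**What the plan says.** Five sections of the protocol article bear on this.

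- **Sequence generation {16a}** has the principal investigator produce the list in Excel: "The randomization sequence, with a block size of four, will be produced using computer-generated random numbers". It is a single running list: "No stratification of participants will be performed in this study".
- **Implementation {16c}**: "The allocation sequence will be generated by the principal investigator, and participant enrolment and intervention assignment will be conducted by a co-investigator".
- **Composition of the coordinating centre and trial steering committee {5d}** lists the principal investigator's duties differently: "Supervises the trial, conducts trial registration and participant enrolment, obtains informed consent".
- **Who will take informed consent? {26a}** has the principal investigator inform every participant and obtain written consent before enrolment.
- **Concealment mechanism {16b}** places assignment after the baseline assessment, for those found eligible. An allocator, not further identified there, logs IDs in a spreadsheet and gives each participant the group in a sealed envelope. The section adds that "recruitment staff, data collectors, and statisticians will remain blinded to the group and will not have access to allocated information".

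Intervention description {11a} is relevant to the remedy: "DTT will be conducted with a group of approximately 30 participants".

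**The concern.** Concealment works only if nobody who influences a person's entry into the trial can know or infer that person's assignment. Here two sections name different people as enroller. The person who writes the sequence also takes consent, and the person who assigns may also enrol. The envelope, as described, tells the participant the group. Nothing stated keeps the list from whoever consents or enrols.

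The risk is selection bias. The comparator is usual daily activity, and participants and providers are not blinded. Entry also requires that a person can attend twice a week for four weeks, which leaves room for judgement and encouragement. Someone who expects a given arm could press more or less hard for consent or enrolment. Blinded outcome assessment does not prevent this. ANCOVA on age, sex and baseline value removes only part of it, because motivation and general fitness are not among the covariates. With 60 participants, a few steered entries could matter.

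**Working it through.** **1. Roles set side by side**

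| Task | {16a} and {16c} | {5d} | {26a} |
|---|---|---|---|
| Generate sequence | Principal investigator | – | – |
| Take consent | – | Principal investigator | Principal investigator |
| Enrol | Co-investigator | Principal investigator | – |
| Assign | Co-investigator | – | – |

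The row for enrolment contradicts itself.

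- If {5d} governs, the author of the sequence takes consent and enrols.
- If {16c} governs, the co-investigator enrols and assigns, and the author of the sequence still takes every consent under {26a}.

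On both versions the author of the sequence takes part in bringing people into the trial. That person could know 60 of 60 assignments.

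**2. What the block of four adds, if allocation runs alongside enrolment**

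Inputs: block size 4 ({16a}), ratio 1:1 (Trial design {8}), no stratification ({16a}), total 60 (Sample size {14}), hence 60 / 4 = 15 blocks. There are 6 equally likely orders of two A and two B.

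Assignments that are certain from the earlier ones in the block:

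- AABB and BBAA: the third and fourth are certain, 2 each.
- ABAB, ABBA, BAAB, BABA: only the fourth is certain, 1 each.

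Mean per block = (2 × 2 + 4 × 1) / 6 = 8/6 = 4/3. As a share, (4/3) / 4 = 33.3%. Over the trial, 15 × 4/3 = 20 of 60.

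Expected correct guesses by someone who sees earlier assignments and always guesses the arm with more places left:

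- first place 1/2
- second place 2/3
- third place 1/3 × 1 + 2/3 × 1/2 = 2/3
- fourth place 1

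Sum = 1/2 + 2/3 + 2/3 + 1 = 17/6 per block. As a share, (17/6) / 4 = 70.8%, or 15 × 17/6 = 42.5 of 60, against 50% under full concealment.

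**3. Does block size drive the problem?** The same enumeration gives, for a fixed block of 6, 25.0% certain and 68.3% guessed correctly; for 8, 20.0% and 66.6%. A larger fixed block helps little, so roles and timing matter more.

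**4. Sample size.** The stated numbers reproduce and are not in dispute. The exact two-sample t-test (two-sided 0.05, power 0.80) gives 16.71, rounded up to 17 per arm, for TMT-A (15 s, SD 15 s) and 25.52, rounded up to 26 per arm, for TMT-B (20 s, SD 25 s). Nothing here changes them.

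**The case against.** A reader might infer four stronger conclusions, which the article does not support.

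- **That concealment has failed.** Assignment follows baseline testing and the eligibility check, and sealed envelopes are used. The article does not say who prepares the envelopes or who holds the list, and such custody details may stand in the full protocol. That the co-investigator sees past assignments is an inference from the assigning role. What stands is that the stated roles do not assure concealment.
- **That {16b}, {16c} and {5d} cannot all be true.** The direct conflict is between {16c} and {5d}. The recruitment staff in {16b} may be other people, since Recruitment {15} describes advertisements and flyers and {16b} mentions the allocator separately. The assurance in {16b} fails for the principal investigator and co-investigator only if they count as recruitment staff.
- **That 20 of 60 allocations are predictable without condition.** This needs allocation one by one during enrolment. The wording of {16b}, training in a group of about 30 and the short recruitment window are all compatible with a single batch. In that case prediction from past assignments largely disappears. The figure also measures predictability; it is not a bias in seconds or a change in type I error.
- **That the TMT-A entry window can be bent to suit the arm.** It is a timed test. {5d} gives the attention assessments to data collectors, and {17a} blinds them. Consent and enrolment decisions are the more plausible route.

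None of this removes the contradiction over the enroller, or the fact that the author of the sequence takes consent. Both are positive statements, so condensation into an article does not explain them.

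**Conclusion.** The concern holds as a risk that the protocol creates through its own role descriptions. {16c} and {5d} contradict each other on who enrols, and on either version the author of the sequence takes consent. That person could know every allocation. The further figure of about one third (20 of 60) rests on three assumptions: allocation one at a time during enrolment, sight of earlier assignments, and knowledge of the block size. The article neither states nor excludes the first. No shift in TMT times can be derived from the document, and none is claimed. The sample size and the primary analysis model are unaffected.

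**What to change.** 1. Reconcile {26a}, {16a}, {16b}, {16c} and {5d}. Have an existing team member with no part in consent, eligibility or enrolment generate and hold the sequence, for example the data manager if kept apart from outcome data collection. Name one enroller who has no access to it, and say in {16b} whom the term *recruitment staff* covers.
2. Where still possible, finish consent, eligibility and baseline testing for everyone, freeze the ordered ID list, and then allocate all participants in one batch. This fits the joint training of about 30 people. Batch allocation does not replace the separation of roles: someone who generates a list after baseline data are known could regenerate it or reorder the IDs. Hence the independent generator and the frozen order.
3. Trial status gives 25 September 2025 as the end of recruitment. If allocation has already taken place, correct the text and report who actually generated and held the sequence, took consent, enrolled and assigned, and in what order.

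Cost: changes of wording and a small shift of duties among current staff, with no extra participants and no change to the analysis. With batch allocation, participants learn their group only after the last baseline visit.
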